### Statistical Analysis and Sample Size Calculations

#### Sample Size Calculation

Outcomes are on the individual patient level, and the clustering involves the entire GP clinic, not the individual GP. A balanced design with a common total cluster size and common period effect was adopted. As the study is a superiority trial, results from the feasibility study [16] and Danish national register data will inform the choice of parameters as inputs to the sample size formula derived by Li et al [19]. The intended effect size was fixed at a reduction from 0.32 to 0.28 based on the register results, which approximately corresponds to the distance between the median or mean to the 25th percentile. With a significance level of 0.05, power at 0.8, within-period within-cluster correlation of 0.02, and across-period within-cluster correlation as 0.01 to detect a difference between a prevalence of 0.32 recontacts in the control group and 0.28 in the intervention group, the sample size was calculated as 108 clinics, contributing 50 contacts each in the trial period. Pragmatically, the inclusion of 100 clinics was chosen.

#### Blinding (Masking)

Due to the intervention procedure (an oropharyngeal, nasopharyngeal, or nasal swab) and the use of project specific reimbursement codes, it is not possible to blind the patients and GPs.

#### Outcomes

The primary outcome is modeled as group difference in number of patients with ARI recontacting the GP from the date of the initial contact (day 0) and the following 7 days in the intervention and control periods [19]. Secondary outcomes include safety outcomes such as group difference in the total number of redeemed antibiotic prescriptions (day 0 and following 7 days), the total number of hospital admissions, and deaths (from the date of the initial contact [day 0] and following 14 days) and total treatment costs, productivity costs, quality-adjusted life years, and incremental cost-effectiveness or utility ratio (from day 0-28) [14]. In addition, patient (day 0) and GP satisfaction (after the end of trial) is evaluated along with patients’ health-related quality of life (day 7, 14, and 28). Furthermore, the study elucidates several aspects and factors based on the process evaluations’ qualitative design, which allows us to assess the quantitative outcomes. Where the quantitative outcomes emphasize measured effects, the qualitative design allows insight into, for instance, the participants’ perceptions of diagnostic practices in the clinic, the emergence and coordination of behavior, experiences, and interactions with the device, and thus explains how people use and perceive the device the way they do [16]. Multimedia Appendix 1 describes the different outcomes and points of interest including information on the specific measure, metric, applied instrument, time period, data source, and target population in a table overview.

### Data Collection

#### A Triangulated Design

The evaluation is based on both quantitative and qualitative methods. Quantitative data will be collected from national administrative registries and via web-based questionnaires; qualitative data will be collected via interviews and observations, including video observation (see details in subsequent sections).

#### Questionnaire Data

The GPs or staff will distribute a leaflet with a QR code (and a link) to a web-based survey to all patients with ARI aged ≥15 years. For patients aged <15 years, the caregiver will be asked to answer the questionnaire. In the first questionnaire, the personal identification number and contact information will be collected, and the subsequent questionnaires will be distributed via a link in email and SMS text message at day 7, 14, and 28. In case of nonresponse, reminders will be sent within 2 days. Participants who complete all 4 questionnaires will be entered into a lottery for 1 gift card of Dkr 1000 for completing the first questionnaire and 1 gift card of Dkr 2500 for completing all 4 questionnaires. Questionnaires will be managed via a secure electronic questionnaire system (SurveyXact). Each questionnaire will take approximately 5 to 10 minutes to complete. Furthermore, a questionnaire will be sent to all participating GP clinics at the end of the trial followed by a reminder after 2 weeks in case of no response. The questionnaire will take approximately 5 minutes to complete. In it, the GPs will be asked about their overall experience of the equipment associated with (1) support for performing precise diagnostics, (2) support for clinical judgment, (3) the influence of the test results related to clinical management of patients, (4) the influence of the test results in patient communication concerning their condition, (5) disruption of consultation, (6) disruption in overall workflow, and (7) whether the equipment belongs in general practice. In addition, there is space for the GPs to write comments.

#### Register Data

Comprehensive public register data on contacts and services provided in primary care, prescription of antibiotics, and hospital contacts and various characteristics of the GP clinics will be retrieved from the Danish Health Data Authority [20]. Furthermore, information on morbidity, socioeconomic status, and various demographic characteristics on each patient will be obtained from Statistics Denmark [21]. Data from the different registers are linked by the patients’ personal identification number. No data will be retrieved from the registers until the protocol paper is accepted for publication.

#### Qualitative Data

Qualitative data will be collected through an ethnographic fieldwork, which includes several key components. First, 10 pre- and postintervention interviews will be conducted with GPs and staff across 11 clinics. In addition, participant observations will take place in 5 clinics both before and during the intervention along with video observations in 3 out of the 5 clinics. Furthermore, 14 patient interviews will be held after the intervention.

Interviews with health professionals will focus on value assessments and sense-making processes tied to their experience with diagnostic technologies in general and the POC PCR equipment specifically. Participant observation will be conducted (with and without video-recorded participation) to obtain in-depth knowledge about everyday working life; organizational and communicative behavior; and interactions between health professionals, staff, and patients with (and without) the POC PCR equipment in the GP clinic. Finally, patient interviews will focus on their experience with use of the POC PCR equipment, feelings of diagnostic certainty, and reflections concerning the perceived impact of the POC PCR test on relational and communicative processes.

#### Data Management

Questionnaire data will be collected by SurveyXact and stored on secure servers at University of Southern Denmark. After data cleaning, questionnaire data will be transferred to secure scientific servers at Statistics Denmark and linked to register data via the personal identification number, after which all data will be pseudonymized.

Qualitative data will be collected by means of digital recorders during interviews, by field notes during observations, and using a GoPro video camera (handheld by the researcher) during video observation. After collecting data, they will be stored on secure servers provided by SDU. NVivo software (QSR International) will be used for transcriptions and analytical purposes.

After publication of the study, the data manager will ensure that all study data are deleted.

### Data Analysis

#### Effectiveness of GP Access to POC PCR

Demographic characteristics of the included patients and GP clinics will be presented. Analysis of the binary primary outcome uses a standard logistic regression model on the individual (contact) level, accounting for clustering of patients in clinics by generalized estimating equations. Primary analysis will follow an intention-to-treat approach, and we want to show superiority. A corresponding analysis strategy will be applied for hospital admissions, deaths, and redeemed antibiotic prescriptions. A level of 5% will be set as statistically significant. Analyses will be performed with the most recent version of Stata (StataCorp).

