#### Within-Trial Cost-Effectiveness

The cost-effectiveness analyses will take both a national health care perspective and, separately for the purpose of sensitivity analysis, a limited restricted societal perspective, including health care costs, patient costs (travel cost), and productivity costs for patients or their caregiver (in case the patient is a child aged <15 y). Cost-effectiveness will be reported in terms of the incremental cost-effectiveness ratio (ICER) expressed as the difference in costs divided by the difference in outcome, between patients in the intervention and control groups. Costs will be estimated from the time of initial contact (day 0) and over a follow-up period of 28 days and calculated by category. Due to the short duration of the study, costs and outcomes will not be discounted. Costs will be expressed in Euros, in 2024 conversion rates. Effect will be measured as the total number of recontacts within 7 days and quality-adjusted life years within 28 days. Quality-adjusted life years are calculated as the area under the utility curve for each patient based on patients’ health-related quality of life measured by EQ-5D-5L for patients aged >15 years (in Denmark, individuals become responsible for managing their own health care at the age of 15, therefore not a requiring parental intermediary or proxy completion of the EuroQoL 5-Dimension) and valued using Danish value sets [22,23]. Missing costs or quality-of-life data will be handled by multiple imputations. Differences in mean costs and effect will be estimated using separate generalized linear regression models, with appropriate distribution and link functions for costs and outcomes. The models will control for treatment, time point, treatment-by-period interaction as fixed effects, and cluster at the GP level as a random effect. Furthermore, the models will adjust for baseline health care cost (6 months before the initial contact) and baseline utility [24]. Nonparametric confidence intervals for costs, effect, and ICER will be computed using a 2-stage bootstrapping technique with 1000 replications [25] and the 2.5th and the 97.5th percentile of the 1000 bootstrap replications. Conventional methods for estimating uncertainty around the ICER, such as cost-effectiveness acceptability curves, will be applied as well. Sensitivity analyses will be conducted to test assumptions, uncertainty around variable estimates, and the robustness of results.

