## Results

As per the randomized crossover design carried out during September 2023 to March 2024 investigating a sample of 100 GP clinics, it is expected to get in-depth and multifaceted understanding of the effects of the availability of the POC PCR test equipment in general practice.

Specifically, in terms of effectiveness, costs, and how organizational and experiential factors may work as barriers and facilitators in the uptake of the intervention in the clinic, both quantitative generalizable results and qualitative explanations of contextual conditions are expected.

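### The primary logistic GEE names no period term, although the sample size and the economic models allow for one; a seasonal shift in recontact risk would then widen the interval and cost some power

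*Protocol article*

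**What the plan says.** The Protocol article, section Effectiveness of GP Access to POC PCR, gives the primary model: "Analysis of the binary primary outcome uses a standard logistic regression model on the individual (contact) level, accounting for clustering of patients in clinics". Generalized estimating equations handle the clustering. A corresponding strategy is to be used for hospital admissions, deaths and redeemed antibiotic prescriptions. No covariates are listed, and neither the type of standard error nor the working correlation is stated.

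Two other sections treat period as part of the design:

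- Sample Size Calculation: "A balanced design with a common total cluster size and common period effect was adopted". The inputs separate correlation within a period from correlation across periods: "With a significance level of 0.05, power at 0.8, within-period within-cluster correlation of 0.02, and across-period within-cluster correlation as 0.01".
- Within-Trial Cost-Effectiveness: "The models will control for treatment, time point, treatment-by-period interaction as fixed effects, and cluster at the GP level as a random effect". One of the effects modelled there is the number of recontacts within 7 days.

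The trial is a two-sequence cluster crossover (AB or BA, 1:1) with 7-week inclusion periods separated by a washout, "carried out during September 2023 to March 2024".

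**The concern.** In a two-period crossover, treatment and period are tied together within each clinic. AB clinics have the intervention early and BA clinics have it late. If recontact risk changes between the periods, the within-clinic contrast moves by the size of that change, in opposite directions in the two sequences. A period term removes this movement. Without one, a clinic-level sandwich variance reads it as random variation between clinics. The reported standard error is then larger than the true sampling error, and power is lost that the crossover was chosen to provide. If the two sequences are also unequal in clinics or contacts, the movements no longer cancel and part of the seasonal change enters the treatment estimate.

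The article is also inconsistent with itself. Recontacts are adjusted for period in the economic evaluation but, as written, not where they are the primary outcome. The margin is already thin, because 108 clinics were calculated and 100 chosen.

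**Working it through.** **Inputs.** From Sample Size Calculation: "a prevalence of 0.32 recontacts in the control group and 0.28 in the intervention group"; alpha 0.05 (taken as two-sided); correlations 0.02 within and 0.01 across periods; "the sample size was calculated as 108 clinics, contributing 50 contacts each in the trial period"; "Pragmatically, the inclusion of 100 clinics was chosen". Assumptions: 25 contacts per clinic per period (50 split equally), equal clinic sizes, and a period shift π in recontact risk. No document gives π.

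**1. Reproduce the plan's figure.** With m contacts per period, the variance of one clinic's treatment difference is V × [1 + (m − 1)(0.02) − m(0.01)] / m.

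- At m = 25 the bracket is 1 + 0.48 − 0.25 = 1.23.
- With V = 2 × 0.32 × 0.68 = 0.4352, clinics needed = (t₀.₉₇₅ + t₀.₈)² × 0.4352 × 1.23 / 25 / 0.04². With n − 2 degrees of freedom, the smallest n that satisfies this is 108, as stated.
- Reading 50 as contacts per period gives only 61 to 66 clinics, so 25 per period is the reading that fits.

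**2. Power with a period term.** With V = 0.32 × 0.68 + 0.28 × 0.72 = 0.4192:

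- v = 0.4192 × 1.23 / 25 = 0.0206.
- With 100 clinics, SE = √(0.0206/100) = 0.01436.
- Power = Φ(0.04/0.01436 − 1.96) = Φ(0.825) = 79.5%, whatever the shift.

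**3. Power without it, clinic-robust SE, equal sequences.** The clinic differences move by +π or −π, so the estimated variance per clinic becomes v + π² while the true sampling variance stays at v. The reported SE is multiplied by r = √(1 + π²/v), and power = Φ(2.785 − 1.96 r).

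| Assumed shift (points) | r | Power | Type I error |
|---|---|---|---|
| 0 | 1.00 | 79.5% | 5.0% |
| 2 | 1.01 | 79.0% | 4.8% |
| 4 | 1.04 | 77.4% | 4.2% |
| 6 | 1.08 | 74.6% | 3.4% |
| 8 | 1.14 | 70.6% | 2.5% |
| 10 | 1.22 | 65.4% | 1.7% |

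**4. Simulation check.** Logistic GEE with independence working correlation, robust SE and 2,000 runs per scenario, without versus with the period term:

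- 4 points: power 76.8% vs 79.6%.
- 8 points: power 71.6% vs 80.5%. Mean SE is 0.0786 vs 0.0687, against an empirical SD of about 0.07 in both. The mean log odds ratio is −0.193 vs −0.195.
- 8 points, no treatment effect: type I error 2.6% vs 4.9%.
- No shift: power 79.5% vs 79.9%, so adding the term costs nothing.

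**5. Unequal sequences.** Randomization uses blocks of 10 in two strata. Incomplete last blocks can leave each stratum up to 5 clinics apart, so 45/55 is the extreme case from this cause.

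- The shifts then average to 0.10 × π. At 6 points this is 0.006 in risk, or 0.006/(0.30 × 0.70) ≈ 0.03 on the log-odds scale.
- By simulation, the mean log odds ratio goes from about −0.19 to −0.16, or to −0.22 if the imbalance is reversed. The period term removes this bias.

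**6. If model-based exchangeable SEs were used instead.** A single clinic-level correlation (about 0.015, midway between 0.02 and 0.01) gives a variance factor of 1 − 0.015 = 0.985, where the planned correlations imply 1.23. The SE is √(0.985/1.23) = 0.895 of its true value, and type I error is about 7.9% at 25 contacts per period. This harm runs in the opposite direction and does not depend on a seasonal shift.

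**The case against.** The strongest reply is that the article is silent rather than exclusive. It names a model family and lists no covariates at all, and a full protocol or analysis plan that is not shown may include period. The Outcomes section also cites, for modelling the primary outcome, the same source that the sample size formula comes from, which may imply a model that allows for period. This part stands: a reader might infer that the plan rules out a period term, and the text does not say so. What remains is the mismatch within the article, since period is named for sizing the trial and for the economic models but not for the primary one.

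The second reply concerns size, and it also stands. No shift in recontact risk is given. A shift as large as the whole treatment effect (4 points) costs only 2 to 3 points of power. A changing mix of infections need not change the 7-day recontact proportion much, and a higher winter volume alone would not produce this loss.

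Three stronger readings are tempting and are not supported:

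- **That the primary test is invalid.** With balanced sequences and robust SEs the estimate is essentially unbiased and the test conservative.
- **That type I error could reach 11%.** This needs model-based SEs and 50 contacts per period: 1 + 49(0.02) − 50(0.01) = 1.48, and √(0.985/1.48) = 0.816. The plan's figure reproduces at 25, where the result is about 8%.
- **That unequal clinic sizes make the omission far costlier.** With an assumed size CV of 0.7 and a 6-point shift, simulated power is about 76 to 77% with the term and 67 to 70% without. Part of the fall from 79.5% comes from unequal sizes themselves, not from the missing term.

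**Conclusion.** The point holds as a should-fix. As written, the primary model does not carry the period effect that the sample size assumes and the economic models include. With clinic-robust SEs the cost is lost power: nothing at a zero shift, about 2 points at 4, 5 at 6 and 14 at 10. These figures assume 100 equal clinics with 25 contacts per period and the planned correlations. Bias arises only if sequences or contact numbers are unequal, and is about 0.03 on the log-odds scale at 45/55 clinics and 6 points. That the interval is too wide (robust SEs) and that it is too narrow (model-based exchangeable SEs) are alternatives. Which one applies depends on an SE type that the article does not state.

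**What to change.** In Effectiveness of GP Access to POC PCR, add period (first or second) as a fixed effect to the primary GEE and to the models for antibiotic prescriptions, hospital admissions and deaths. For deaths, which may be rare, add it only where the model can be fitted. State that standard errors are robust and clustered on clinic. Only the main effect of period is needed; a treatment-by-period interaction would change what the treatment coefficient means. Clinic type, the stratification factor, may be added as well. A working correlation that separates within-period from across-period correlation is optional.

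The cost is one sentence, with no loss of power if there is no seasonal shift. The Register Data section says no register data will be retrieved until the protocol paper is accepted, so a change made before then is prespecified. If a separate analysis plan already includes period, the article need only say so.

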### Allocation

The study is designed as a cluster randomized crossover study with the GP clinic as the unit of randomization, that is, all GPs affiliated to a GP clinic are randomized to either intervention (A) in the first period and usual care (B) in the second (AB sequence) or in the BA sequence. Allocation of the general practice clinic is randomized using a computer algorithm and allocation is 1:1 between the AB or BA sequence. When an eligible clinic commits to the trial, the project statistician informs the project management about the next allocation in the allocation sequence and the clinic is randomized according to this, that is, blinded randomization allocation is used.

Randomization at the patient level is not considered feasible, as an ongoing randomization procedure in the clinic would be time consuming and pose a risk of bias and interference with the diagnostic procedure and subsequent decision-making by the GP.

Therefore, randomization is stratified by type of clinic, that is, partnership- or single-physician clinics. Large collaborative clinics are randomized as one unit in the group of non–single-physician clinics. A block randomization in blocks of 10 is used.

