### Strengths and Limitations

First, there is limited possibility to ensure that the patient receives the postcard and fills out the questionnaire, which may hamper studying the patients’ quality of life and satisfaction. Second, the quality of the quantitative data is highly dependent on GPs applying the project specific reimbursements codes to all relevant patients. As coding after each patient contact is everyday routine for Danish GPs, the coding practice itself is not a new task for the participating clinics. However, coding difficulties associated with the new reimbursement codes cannot be ruled out, which may in turn lead to a slight underreporting. Finally, while the POC PCR test equipment allows for conducting 5 ARI tests, the current test portfolio does not allow testing for, for example, pertussis and mycoplasma. As such, it could influence both the professional and patient experience and perception of what is considered quality and precise diagnostics and, by the mere introduction of increased testing that the POC PCR equipment promotes, the introduction of more testing could lead to an overemphasis of testing for the sake of testing. Moreover, it takes 20 minutes to run a test and a consultation in a Danish general practice usually is reimbursed for only 10 minutes. This practical factor may also influence the uptake of the intervention and the experience of the usefulness of the technology, it may even create additional workload in the clinic.

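### The primary logistic GEE does not confine the treatment contrast to within-clinic comparisons, so it is biased if clinics' intervention-to-control coding ratios track their recontact levels

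*Protocol article*

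**What the plan says.** On design, the Allocation section states: "The study is designed as a cluster randomized crossover study with the GP clinic as the unit of randomization". Each clinic follows the AB or BA sequence and so supplies both intervention and control contacts.

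On analysis, the section Effectiveness of GP Access to POC PCR says that the comparison of recontacts "uses a standard logistic regression model on the individual (contact) level, accounting for clustering of patients in clinics by generalized estimating equations". It extends the same strategy to hospital admissions, deaths and redeemed antibiotic prescriptions. It mentions no clinic term, period term or working correlation. The economic models under Within-Trial Cost-Effectiveness do list time point, a treatment-by-period interaction and a random effect for cluster.

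On size, the Sample Size Calculation assumes a balanced design and aims "to detect a difference between a prevalence of 0.32 recontacts in the control group and 0.28 in the intervention group". It uses a within-period correlation of 0.02 and an "across-period within-cluster correlation as 0.01", and reports that "the sample size was calculated as 108 clinics, contributing 50 contacts each in the trial period". The 4-point target is described as one "which approximately corresponds to the distance between the median or mean to the 25th percentile", so the article itself indicates that clinics differ in recontact rate.

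On who enters the analysis, all patients with an acute respiratory infection in each 7-week period are to be included, without a cap, through a code that the GP enters. The clinics are not blinded, and a separate remunerated test code exists only in intervention periods. Strengths and Limitations accepts that "the quality of the quantitative data is highly dependent on GPs applying the project specific reimbursements codes to all relevant patients".

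**The concern.** A crossover earns its efficiency, and its protection against differences between clinics, by comparing each clinic with itself. A marginal contact-level model compares all intervention contacts with all control contacts. If some clinics contribute relatively more intervention contacts than others, the two pooled samples have different mixes of clinics. If those clinics also have a higher or lower recontact rate, the difference in mix appears as a treatment effect even when no clinic's rate changes.

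Sequence randomisation does not prevent this. Every clinic receives the intervention, and its coding ratio arises after allocation under open-label conditions. A period term or the single-physician versus partnership stratum does not remove it either, because neither carries the clinic's own recontact level. At stake are the primary estimate and the antibiotic, admission and death analyses that inherit the model.

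**Working it through.** **1. The plan's own figure.** Inputs from the Sample Size Calculation: rates 0.32 and 0.28, alpha 0.05 (two-sided assumed), power 0.80, correlations 0.02 and 0.01. Read 50 contacts per clinic as m = 25 per period.

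- Design factor: 1 + (m − 1) × 0.02 − m × 0.01 = 1 + 0.48 − 0.25 = 1.23.
- Clinics: K = (1.96 + 0.8416)² × V × 1.23 / (25 × 0.04²).
- With the control-rate variance in both periods, V = 2 × 0.32 × 0.68 = 0.4352 and K = 105.0. With t quantiles K is 108, the stated figure. Unpooled variances give 102 to 104.
- Taking m = 50 per period gives only 61 to 66 clinics, so 50 is the two-period total.

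The cited formula itself could not be consulted.

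At the 100 clinics chosen, with balanced periods and a mean rate of 0.30 (variance 0.21), the standard error of the risk difference is √(2 × 0.21 × 1.23 / (25 × 100)) = 0.0144, and power is 79.5%. With equal period numbers in every clinic, the GEE and a clinic-conditioned analysis give the same estimate and the same power.

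**2. Spread between clinics.** From the across-period correlation, the SD is √(0.01 × 0.2176) = 0.047. The percentile distance gives 0.04 / 0.6745 = 0.059 if rates are normal, but that includes sampling noise. The smaller value is used below.

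**3. Expected bias under independence.** Let s be a clinic's share of contacts in its intervention period (mean 0.5) and u its deviation in recontact rate. The pooled difference with no treatment effect is 2Cov(s,u) + 2Cov(s,u) = 4Cov(s,u). Since the SD of s is about one quarter of the SD of the log coding ratio, bias ≈ r × SD(log ratio) × SD(clinic rate).

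- r = 0: zero.
- r = 0.3, SD 0.3: 0.3 × 0.3 × 0.047 = 0.004.
- r = 0.5, SD 0.5: 0.5 × 0.5 × 0.047 = 0.012.

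**4. Exchangeable correlation.** A weighted least-squares calculation with share SD 0.10 gives:

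| r | Independence | Exchangeable | Clinic-conditioned |
|---|---|---|---|
| 0 | 0.0000 | 0.0000 | 0 |
| 0.3 | 0.0054 | 0.0031 | 0 |
| 0.5 | 0.0090 | 0.0052 | 0 |

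Nested-exchangeable correlation gives the same values as exchangeable. The ratio 0.0052 / 0.0090 is about 0.58, so the range 0.4 to 1.2 points under independence becomes about 0.2 to 0.7.

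**5. Type I error.** With bias b and SE 0.0144, the rejection rate under no effect is Φ(−1.96 + b/SE) + Φ(−1.96 − b/SE). For b = 0.002, 0.004, 0.007 and 0.012 this is 5.2%, 5.9%, 7.8% and 13.3%. The last falls to 12.5% with an SE of 0.0151, as implied by the 75.7% power at 70/30 splits in step 7. Simulations with 100 clinics, about 25 contacts per clinic-period and a period term gave 8% to 12% with independence and 5% to 8% with exchangeable at r = 0.5. One run of 300 replicates gave 9.0% with exchangeable, with a Monte Carlo error of about 1.7 points. Adding the clinic's intervention share brought the bias to about zero (0.0 to 0.1 points) and rejections to 4% to 6%.

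**6. Imbalance without the correlation.** In a separate logistic simulation under no effect, random imbalance gave a mean log odds ratio of −0.006 (Monte Carlo error about 0.006) and 4.7% rejections. A uniform 65/35 coding excess under intervention gave 0.001. For share SD 0.10, chance leakage over 100 clinics has SD 4 × 0.10 × 0.047 / √100 = 0.0019, small beside 0.0144 and covered by the robust standard error.

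**7. Power cost.** For a true 4-point effect:

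| Split | Independence | Exchangeable | Clinic-conditioned |
|---|---|---|---|
| 50/50 | 79.5% | 79.5% | 79.5% |
| 60/40 | 78.5% | 78.9% | 78.2% |
| 70/30 | 75.7% | 77.1% | 73.7% |

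**The case against.** A population-averaged GEE is a legitimate choice for this design. The article names the model class without closing off covariates, a period term or a working correlation, and a statistical analysis plan that is not shown may supply them. The correlation on which the bias depends is not documented: nothing shows that high-recontact clinics would code relatively more, or fewer, patients under intervention. The inclusion code is the same in both periods, and the article expects only slight under-reporting. That the paid test code prompts more inclusion coding is an inference.

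Most of this stands, and it rules out several stronger readings. A reader might infer that any difference in period numbers biases the result; step 6 shows that it does not.

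A reader might also take an illustrative case as typical: 50 clinics at 0.28 coding 25 and 25, and 50 at 0.36 coding 25 under control and 35 under intervention. The pooled rates are (25 × 0.28 + 35 × 0.36) / 60 = 0.3267 against 0.3200, a false difference of 0.67 points. But there the ratio is perfectly aligned with the clinic's rate, and 0.36 is not a figure from the article. Type I error of 11% to 23% can be produced, but only with independence and 100 contacts per clinic-period, four times the planned number.

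The objection does not remove the point. The model class is a stated choice, the usual working correlations reduce the bias without eliminating it, and a period term was already included in the simulations. It is also fair that which patients are coded may be the larger threat; conditioning on clinic does not address that.

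**Conclusion.** The point holds conditionally. As stated, the primary model does not restrict the treatment contrast to within-clinic comparisons, and the balance under which this would not matter is assumed in the sample size but not secured by the conduct of the trial. Random imbalance, a common seasonal shift or a uniform coding excess under intervention causes no systematic bias.

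Bias in either direction follows if the coding ratio varies between clinics and tracks their recontact level. For r of 0.3 to 0.5 and an SD of the log ratio of 0.3 to 0.5, it is roughly 10% to 30% of the 4-point target with independence (0.4/4 to 1.2/4) and 5% to 18% with exchangeable correlation (0.2/4 to 0.7/4). Both ranges are assumptions, and the article gives no figure for either. It does not support a claim that the result will be biased, or in which direction. The change is worth making because it is cheap and removes the dependence on an unverifiable condition.

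**What to change.** Keep the contact-level logistic GEE with clinic-robust standard errors. Add period and each clinic's own share of intervention contacts as covariates, and report the treatment coefficient, which is then a within-clinic contrast. At the least, prespecify this model as a sensitivity analysis beside the primary one. Do the same for antibiotic prescriptions and admissions. State the working correlation.

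If clinic fixed effects or conditional logistic regression is preferred, use clinic-robust standard errors: model-based ones gave 6% to 12% rejections under no effect. The conditional odds ratio differs from the marginal one by about 1% at these correlations.

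The cost is two covariates and a sentence in the analysis plan, with no new data. Power falls by about 0 to 2 points at moderate imbalance. At 70/30 splits the loss is 2.0 points against independence (75.7 − 73.7) and 3.4 against exchangeable (77.1 − 73.7). Clinics with contacts in only one period add nothing to the contrast. The change does not correct for differences between periods in which patients are coded; that needs its own check.
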